# **1.Introduction**

Visual fatigue, or asthenopia, occurs when visual demands exceed the capacity of the visual system, leading to various ocular discomfort and systemic symptoms. This condition can negatively affect personal activities, quality of life, and work productivity.^1,2^ The increasing prevalence of asthenopia underscores its growing significance as a public health issue.^3^ In a study of Chinese ophthalmologists, over 40% experienced visual fatigue, with presbyopia identified as a major risk factor.^4^ Moreover, in a study of presbyopic computer workers, all participants reported experiencing at least one symptom of visual fatigue.^5^ Given the high prevalence of asthenopia in presbyopic population, finding effective methods to alleviate these symptoms is crucial.

Previous studies have demonstrated that exposure to red light wavelengths may alleviate symptoms of visual fatigue, such as eye redness and dry eye^6^, and may also support retinal health through neuroprotective effects^7^. Additionally, studies have shown that improvements in ocular microcirculation have been significantly associated with the relief of asthenopia.^8,9^ Repeated low-level red-light therapy (RLRL) can significantly increase ocular blood flow. Several studies consistently reporting a 10-20% thickening of the posterior choroid following red light therapy.^10-13^ The effect of RLRL on increasing choroidal blood flow has also been validated in myopic adults. In our preliminary study, we conducted a crossover randomized controlled study involving 37 adult myopic patients who underwent one month of RLRL treatment (ClinicalTrials.gov identifier: NCT05747742). The results showed a significant increase in peripapillary choroidal thickness (pChT), macular choroidal thickness (mChT), and the density of the peripapillary deep capillary plexus (DCP) compared to baseline (Figure 1). These findings suggest that RLRL improves ocular blood flow, potentially alleviating visual fatigue. Moreover, photobiomodulation (PBM), which incorporates the use of red light, has been shown to enhance regional cerebral blood flow, as well as improving mood, memory, and cognitive function.^14,15^ Despite these potential benefits, no research to date has explored the use of red light therapy specifically for alleviating visual fatigue in individuals with presbyopia.

In this study, we aim to evaluate the effects of RLRL therapy on alleviating visual fatigue in individuals with presbyopia over a one-month period. Additionally, we will assess the potential benefits on accommodation function, near visual ability, cognition, and emotional effects of RLRL in this population.

Figure 1. Changes in Choroidal Thickness and Capillary Density During One Month of RLRL Therapy

[figure not shown]

# **2. Study Objectives**

## 2.1 Hypothesis

RLRL therapy will effectively alleviate symptoms of asthenopia and well-being in individuals with presbyopia.

## 2.2 Study Aims

- To evaluate the effectiveness of RLRL therapy in reducing symptoms of asthenopia.
- To assess the impact of RLRL therapy on accommodation function, near visual ability, cognition, and emotional well-being in individuals with presbyopia.

## 2.3 Outcome Measures

### Primary Outcome

The primary outcome was the change in Computer Vision Syndrome Questionnaire (CVS-Q) score at the 31-day follow-up visit. ^16^ These scores will be derived from the Computer Vision Syndrome Questionnaire (CVS-Q), a widely recognized tool for assessing subjective symptoms of asthenopia.

### Secondary Outcomes

- Change in accommodation function, including accommodation amplitude (AA), facility of accommodation (AF), binocular cross-cylinder response (BCC), positive and negative relative accommodation (PRA, NRA), and accommodative convergence-to-accommodation (AC/A) ratio at 1 month compared to baseline.
- Change in near visual ability, including Near Activity Visual Questionnaire (NAVQ) score^17^, habitual near visual acuity (HNVA), near-addition power (ADD) at 1 month compared to baseline.
- Change in critical flicker fusion frequency (CFF) and other objective asthenopia indicators (e.g., eye movement, pupil parameters, and blink patterns) at 1 month compared to baseline.
- Change in cognition function, measured by EEG and the Montreal Cognitive Assessment Scale (MoCA)^18^ at 1 month compared to baseline.
- Change in self-reported emotional states, assessed by the Positive and Negative Affect Schedule (PANAS-X)^19^ at 1 month compared to baseline.

# **3. Study Population**

## 3.1 Recruitment Procedure

Interested individuals will be invited to the PolyU Optometry Clinic for eligibility screening. The research team will assess prospective participants through a series of evaluations, including visual acuity tests, slit lamp examinations, accommodation function examinations, fundus examinations, and a review of their medical history. Those who meet the eligibility criteria will proceed with the study procedures.

## 3.2 Inclusion Criteria

- Individuals aged over 40 years old.
- Self-reported symptoms of visual fatigue.
- Diagnosis of presbyopia, defined as near visual acuity that does not meet an individual’s needs despite optimal distance correction.
- Require near correction in daily life.
- No light therapy received in the past six months.
- Giving informed written consent.

## 3.3 Exclusion Criteria

- Presence of diseases that can cause eye pain or headaches, such as strabismus, glaucoma, ocular trauma, conjunctivitis, migraines, keratitis, iridocyclitis, or other self-reported diseases.
- Systemic diseases (e.g., epilepsy, photosensitivity, seizure) or illiteracy.
- Severe cataract.
- Afterimage time longer than 6 minutes.

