## 4.2 Randomization and Masking

Eligible participants will be randomly assigned in a 1:1 ratio to either the intervention group or the control group, using a computer-generated randomization sequence. The intervention group will undergo RLRL therapy, while the control group will use a sham device, which operates at only 10% of the active device’s power. The light power through a 4-mm pupil is 0.29 mW for the RLRL device and 0.03 mW for the sham device. This therapy will be administered using a desktop semiconductor therapy device developed by Eyerising International Pty Ltd, based in Sydney, Australia.

Group assignments were concealed using opaque, sealed, and sequentially numbered envelopes. Each participant was assigned a number according to the order of enrollment, and the corresponding envelope was opened at the time of allocation to determine group assignment. Participants, optometrists, ophthalmologists, clinical examiners, and statisticians were all masked to the treatment allocation. However, if a participant experiences severe adverse reactions, the blinding may be lifted after the investigator determines that unblinding is necessary.

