## 4.5 Study Methodology

### 4.5.1 Study Procedure

- Eligibility: The research team will conduct visual acuity tests, slit lamp examinations, accommodation function examinations, and fundus examinations on the subjects to verify their eligibility for the study. Then informed consent will be obtained from the eligible subjects. Sociodemographic information and general health history will also be recorded.
- Asthenopia measurement: The asthenopia questionnaire scores will be derived from the Computer Vision Syndrome Questionnaire (CVS-Q), a widely recognized tool for assessing subjective symptoms of asthenopia. Change in CFF and other objective asthenopia indicators (e.g., eye movement, pupil parameters, and blink patterns) will be measured by a non-invasive eye tracker at 2 weeks and 1 month compared to baseline.
- Accommodation function: AA, AF, BCC, NRA, PRA, and AC/A ratio will be evaluated by optometrists at baseline, 2 weeks, and 1 month.
- Near visual ability: The NAVQ scores will be derived from the Near Activity Visual Questionnaire, a widely recognized tool for assessing near-vision functioning in presbyopia. HNVA was assessed at 40 cm using a near LogMAR chart under the participant’s habitual near correction. ADD was determined as the minimum additional lens power required to achieve best near visual acuity under full distance correction.
- Visual acuity: Best-corrected distance visual acuity (BCDVA) and best-corrected near visual acuity (BCNVA) at 40 cm will be measured at baseline, 2 weeks, and 1 month.
- Cognitive tests: Cognition function will be measured by EEG and the MoCA at baseline, 2 weeks, and 1month.
- Emotional states: Self-reported emotional states will be assessed by the PANAS-X at baseline, 2 weeks, and 1 month.
- Fundus Examinations: At baseline, 2 weeks and 1 month, participants will undergo non-invasive fundus examinations using Optical Coherence Tomography (VG200) and Laser Speckle Flowgraphy (LSFG-NAVI).

The data collected for the baseline visit and the follow-up visits are showed in Table 1.

Table 1. Time and Events Schedule for Study Procedures

|  | **Visit 1 (baseline examinations)** | **Visit 2 (2 weeks)** | **Visit 3 (1month)** |
| --- | --- | --- | --- |
| Pre-screening criteria | √ |  |  |
| Informed consent | √ |  |  |
| Non-cycloplegic refraction | √ |  |  |
| Slit lamp examination | √ |  |  |
| BCDVA | √ | √ | √ |
| BCNVA | √ | √ | √ |
| HNVA | √ | √ | √ |
| EEG | √ | √ | √ |
| MoCA scale | √ | √ | √ |

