# **5. Participants Safety and Withdrawal**

## 5.1 Risk Management and Safety

The primary risk of the intervention is related to the low-level red-light therapy. The RLRL therapy device (Eyerising International Pty Ltd, Melbourne, Australia) is a semi-conductor laser product, with a power of 0.29 mW for a 4-mm pupil. It holds CE certification in the European Union, MHS registration in Malaysia, TGA approval in Australia, MHRA approval in the UK, medical device registration in Turkey, Medsafe registration in New Zealand, and a certificate from the National Medical Products Administration (NMPA) in China for myopia treatment. The manufacturer is certified under the ISO 13485 quality management system for medical device production. The device is widely available and commonly used for amblyopia treatment. Studies on the efficacy of RLRL for juvenile myopia control have been conducted in China, with no reported ocular complications or adverse effects in clinical trials.

Common side effects of the light therapy device include flash blindness, short-term glare, and afterimages, which typically resolve after a few minutes of eye closure. The examinations in this study are standard clinical procedures widely used in practice and research, posing minimal to no risk.

Adherence to task guidelines will be closely supervised, with active monitoring for adverse events. Any incidents will be promptly documented and addressed. Safety data, including discomfort, side effects, or health concerns, will be systematically collected and reviewed. Participants will be fully informed of potential risks and safety protocols.

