## 5.2 Handling of Withdrawals

Study participation will be terminated by an investigator for the following reasons:

1. Any severe adverse event, such as a sudden loss of vision greater than two lines or the development of a central visual field scotoma.
2. The participant meets an exclusion criterion (either newly developed or previously unidentified) that precludes further involvement.
3. Any other reason deemed appropriate by the investigator.
4. New safety information necessitates halting the study.

Participants may withdraw from the study at any time upon request. Those who withdraw will be asked about their reasons and whether permission is granted to use data collected prior to withdrawal. If permission is denied, all associated data will be deleted from the system.

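### The afterimage limit depends on light exposure and can also end participation after randomisation, so day-31 data may be lost unevenly between the arms

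*Protocol*

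**What the plan says.** The exclusion criteria in Protocol section 3.3 include "Afterimage time longer than 6 minutes". No light source, exposure, assessor or time point is attached.

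Two places list the eligibility examinations. Section 3.1 describes evaluations "including visual acuity tests, slit lamp examinations, accommodation function examinations, fundus examinations, and a review of their medical history". Section 4.5.1 states: "The research team will conduct visual acuity tests, slit lamp examinations, accommodation function examinations, and fundus examinations on the subjects to verify their eligibility". Neither mentions an afterimage test. Table 1 has no afterimage row, only a general pre-screening row at Visit 1. On the order of steps, section 4.5.1 adds: "Then informed consent will be obtained from the eligible subjects".

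Section 5.2 lists the reasons for which an investigator ends study participation. The second is: "The participant meets an exclusion criterion (either newly developed or previously unidentified) that precludes further involvement".

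Section 5.1 says of the intervention: "Common side effects of the light therapy device include flash blindness, short-term glare, and afterimages". Section 4.2 gives the control group a "sham device, which operates at only 10% of the active" device's power, that is 0.03 mW against 0.29 mW through a 4-mm pupil, and states that participants are masked.

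Section 6.3 plans an intention-to-treat analysis of everyone randomised, a per-protocol analysis of those who completed both follow-up visits, and mixed-effects models for the repeated measures. Section 5.3 rules out replacing dropouts.

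**The concern.** Most of the exclusion criteria describe a disease or a history that exists before allocation and has nothing to do with the arm. Afterimage time is different. It can be observed only after exposure to light, and the trial's own intervention is such an exposure. A criterion of this kind is harmless if everyone is tested the same way before allocation. It becomes a problem if it is met for the first time on the allocated device, because meeting it is then partly an effect of treatment.

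Section 5.2 allows exactly that. An exclusion criterion that develops or is discovered after entry is a reason to end participation altogether. If this happens more often on the active device, the arms lose day-31 CVS-Q scores at different rates for a treatment-related reason, and the comparison of those who remain is no longer protected by randomisation.

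**Working it through.** **1. When is the criterion assessed?** Section 3.3 makes it an eligibility criterion, and sections 3.1, 4.1 and 4.2 randomise only eligible people, so assessment before allocation is clearly intended. No listed examination measures it, and no stimulus is given. The test is unspecified. Section 4.5.1 also places consent after eligibility is verified, so a light-exposure test done in that order would come before consent.

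**2. What happens if it is first met after allocation?** The second termination reason in section 5.2 covers all exclusion criteria, including those newly developed or previously unidentified. A long afterimage first noticed during home use fits that wording. The stated consequence is the end of study participation.

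**3. Would this be related to the arm?** Section 5.1 names afterimages as a side effect of the device. Relative power of the sham: 0.03 / 0.29 = 0.103, about 10%. A higher frequency in the active arm is plausible, but the documents give no rate for either arm.

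**4. What is lost?**
- Primary outcome: no CVS-Q at day 31. If termination precedes Visit 2, only the baseline score exists.
- Per-protocol set: anyone terminated before the 1-month visit is out by definition.
- Intention-to-treat set: nobody is formally removed. The mixed model uses the scores already collected, and the loss enters as missing data.

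**5. The plan's own sample size.** Inputs from section 6.1: d = 0.80, two-sided alpha 0.05, power 80%, 15% loss. For a two-sample t-test the noncentrality is d / √(1/n₁ + 1/n₂). With 26 per group this is 0.80 / √(2/26) = 2.88 on 50 degrees of freedom, giving power 0.807; 25 per group gives 0.791. So 26 is right. Inflation: 26 / (1 − 0.15) = 30.6, rounded up to 31 per group, 62 in total. The plan's figures reproduce and the point does not change them.

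**6. Precision, under assumed losses.** Suppose the afterimage rule removes a further share of the 26 evaluable active participants, on top of the planned 15%, and none on sham, with d still 0.80 among those who remain. Counts are rounded down.

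| Assumed extra active-arm loss | Active / sham | Power |
|---|---|---|
| 0% | 26 / 26 | 0.807 |
| 5% | 24 / 26 | 0.791 |
| 10% | 23 / 26 | 0.782 |
| 20% | 20 / 26 | 0.749 |
| 30% | 18 / 26 | 0.722 |

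These shares are assumptions, not document figures. The loss of power is modest across the range.

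**7. Bias.** In a comparison of completers, the shift is f × δ, where f is the share of the active arm removed and δ is the difference in mean outcome between those kept and those removed. The documents give neither f nor δ, and δ may have either sign.

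**The case against.** The strongest reply is that the protocol already screens before it allocates, and that an afterimage check may simply sit within the general pre-screening row of Table 1. The list in section 3.1 is introduced as examples, and the medical-history review has no row of its own either. That stands: a reader might infer that no pre-randomisation test exists, but the text shows only that the test is not described.

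Secondly, termination applies only to a criterion that precludes further involvement, which leaves the investigator some discretion. That also stands, so termination is possible rather than automatic. But the discretion would be exercised on a symptom that itself hints at allocation, so it is not a safeguard against uneven loss.

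Thirdly, intention-to-treat already includes everyone randomised. Correct: a reader might infer that active participants are dropped from the main analysis, and section 6.3 says otherwise. What remains is missing follow-up in that analysis and exclusion from the per-protocol set.

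Fourthly, a reader might infer that screening shows everyone the active light and so helps them recognise the sham. No section says which light is used. A neutral or sham-level light before allocation would avoid both this and the selective loss. The masking concern is therefore conditional on the active light being chosen.

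**Conclusion.** The point holds as a limited one. An exclusion criterion tied to light exposure has no stated time or stimulus, and section 5.2 as written can turn it into an arm-related reason for ending follow-up. The consequence is uneven loss of day-31 CVS-Q data and of per-protocol membership, not removal from the intention-to-treat set.

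This rests on two assumptions: that some participants first exceed the limit after randomisation, and that this is more frequent at full power than at about 10% of it. The second is plausible from sections 4.2 and 5.1 but is not quantified anywhere.

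It is tempting to conclude that the result would be biased in favour of the device. The documents do not support that. Nothing says that people with long afterimages benefit less; if they benefit more, losing them works against the device. Size and direction are both undetermined. The case for acting is that the change costs little and replaces a rule that can create treatment-related missing data.

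**What to change.** Reconcile sections 3.3 and 5.2 and Table 1:

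- **Table 1 and section 4.5.1:** state that afterimage eligibility is assessed at Visit 1, after consent and before the allocation envelope is opened, with one common, stated light exposure for every candidate, and that the time is recorded.
- **Section 5.2:** state that a participant who exceeds the limit only after randomisation is still invited to the scheduled outcome visits and analysed in the intention-to-treat set. This concerns data collection only. The threshold itself and any decision about device use remain with the sponsor.
- **If the active light is used at screening:** ask each participant to guess their allocation after completing the day-31 CVS-Q, and report the guesses by arm.

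The cost is a few minutes per person at Visit 1, outcome visits for a few participants who may have stopped using the device, and possibly one extra question. The sample size does not change.

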## 3.4 Consent

In this study, the informed consent procedures and related documentation must first be approved by the ethics committee. This consent process will ensure eligible subjects are fully informed about the study's purpose, procedures, potential benefits, and risks. Researchers will thoroughly explain the nature of the study, with a focus on aspects related to visual fatigue in individuals with presbyopia.

Subjects will be encouraged to ask any questions they may have about the study, its methods, and its objectives, both before enrollment and throughout their participation. They will be clearly informed of their right to withdraw from the study at any point, without needing to provide a justification for their decision. Ensuring that the participants understand their involvement and rights within the study is a priority, to maintain ethical standards and participant comfort.

# **4. Study Design**

## 4.1 Study Type and Design

This prospective, randomized controlled study will enroll individuals aged 40 years or older who have asthenopia and presbyopia. The study aims to evaluate the effectiveness of RLRL therapy in reducing asthenopia and presbyopia symptoms, as well as its impact on cognitive function and emotional well-being.

Eligible participants will be randomly assigned in a 1:1 ratio to either the intervention group or the control group. Each participant in the intervention group will be provided an RLRL therapy device, which they are required to use twice daily for 3 minutes per session, with a minimum interval of 4 hours between sessions, 7 days a week for one month. Participants in the control group will receive a sham device, following the same usage schedule. The study will evaluate changes in asthenopia questionnaire scores, near visual ability, other objective asthenopia indicators, accommodation function, cognitive function, and emotional states at 2 weeks and 1 month compared to baseline.

## 4.2 Randomization and Masking

Eligible participants will be randomly assigned in a 1:1 ratio to either the intervention group or the control group, using a computer-generated randomization sequence. The intervention group will undergo RLRL therapy, while the control group will use a sham device, which operates at only 10% of the active device’s power. The light power through a 4-mm pupil is 0.29 mW for the RLRL device and 0.03 mW for the sham device. This therapy will be administered using a desktop semiconductor therapy device developed by Eyerising International Pty Ltd, based in Sydney, Australia.

Group assignments were concealed using opaque, sealed, and sequentially numbered envelopes. Each participant was assigned a number according to the order of enrollment, and the corresponding envelope was opened at the time of allocation to determine group assignment. Participants, optometrists, ophthalmologists, clinical examiners, and statisticians were all masked to the treatment allocation. However, if a participant experiences severe adverse reactions, the blinding may be lifted after the investigator determines that unblinding is necessary.

## 4.3 Intervention Compliance Monitoring

Each participant will receive an RLRL therapy device or a sham device and must log in with their unique account details before each treatment session. The device is connected to a centralized system via the internet, allowing for remote monitoring of treatment data and compliance. Two staff members from the project team will review treatment compliance and usage statistics weekly.

